## Abstract

**Background:**

Individuals of African descent are at higher risk of developing kidney disease than their European counterparts, and HIV infection is associated with increased risk of nephropathy. Despite a safe renal profile in the clinical trials, long-term use of tenofovir disoproxil fumarate (TDF) has been associated with proximal renal tubulopathy although the underlying mechanisms remain undetermined. We aim to establish the prevalence of and risk factors for TDF-induced kidney tubular dysfunction (KTD) among HIV-I and II individuals treated with TDF in south-west Nigeria. Association between TDF-induced KTD and genetic polymorphisms in renal drug transporter genes and the *APOL1* (Apolipoprotein L1) gene will be examined.

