**Discussion:**

In spite of TDF being the most commonly used antiretroviral agent and a key component of many HIV treatment regimens, it has potential detrimental effects on the kidneys. This study will establish the burden and risk factors for TDF-induced KTD in Nigerians, and explore associations between KTD and polymorphisms in renal transporter genes as well as *APOL1* risk variants. This study may potentially engender an approach for prevention as well as stemming the burden of CKD in sub-Saharan Africa where GDP per capita is low and budgetary allocation for health is inadequate.

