## Methods/design

Primary outcomes of interest in this study are the prevalence of KTD and the association of polymorphisms in selected candidate SNPs in genes encoding tubular transporters and *APOL1* with KTD. Secondary outcomes include the presence of elevated retinol binding protein (RBP) levels (defined as retinol-binding protein/creatinine ratio > 2.93 μg/mmol) [25] and urinary N-acetyl-beta-D-glucosaminidase (NAG) levels (NAG > 5.93 U/g Cr).

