### Setting and study population

The study will be conducted at the Department of Internal Medicine, Ladoke Akintola University of Technology Teaching Hospital (LTH), Osogbo, Nigeria and the Department of Internal Medicine Research Laboratory, University of the Witwatersrand, Johannesburg, South Africa. Participants will be recruited from ART clinics in Nigeria including LTH (Osogbo), Jaleyemi Catholic Hospital (Osogbo), Osun State Hospitals (Asubiaro, Ede, Ikire, Iwo, and Ila Orogun), Adeoyo State Hospital (Oyo State) and Seventh Day Adventist Hospital (Ile-Ife).

For the case-control phase of the study, PLWHIV on a TDF regimen under regular follow up for at least 3 months at the ART clinics who developed proximal KTD will be designated as cases. Research has shown that the median time to nephrotoxicity after TDF initiation is 3.6 months [8], hence, the rationale for a minimum of 3-months on TDF. The controls will be PLWHIV on a TDF regimen under regular follow up for ≥3 months at the ART clinics showing none of the abnormalities suggesting proximal KTD. The cases will be matched one-to-one to controls by gender, age (+/− 5 years), and TDF duration (+/− 3 months) and will be done on an ongoing basis during recruitment of study participants.

Participants meeting the inclusion criteria will be PLWHIV, aged 18 years and above, receiving TDF-containing therapy, on regular follow up for a minimum of 3 months with a viral load of less than 200 copies/ml. The rationale for the use of 3 months cut off point for the duration of tenofovir treatment was based on the results of a previous study by Brennan et al. [8] that showed that the median time to nephrotoxicity after initiation of TDF was approximately 3 months.

The following individuals will be excluded from the study: Individuals with incomplete history of antiretroviral treatment, including HIV treatment status (either treatment-naïve or experienced), date of commencement of ART and combination of ART); persons who are pregnant or lactating; persons with an estimated glomerular filtration rate (eGFR) < 60 ml/min/1.73m^2^ (eGFR will be calculated by Chronic Kidney Disease Epidemiology Collaboration [CKD-EPI] from serum creatinine estimated during the month enrolled in the study); persons with glomerulonephritis, including IgA Nephropathy and Lupus Nephritis; heart failure (NYHA 3 & 4), malignancy and non-Nigerians.

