### Statistical analysis

Descriptive results of continuous variables will be expressed as medians and interquartile ranges. Continuous variables will be tested for normality using the Shapiro–Wilk test and compared using the student’s *t* test or Wilcoxon rank sum test, as required. For the comparison of proportions, the Chi-square test will be used, with Fisher’s corrections applied when needed. Multivariate logistic regression analyses will be performed to identify factors associated with KTD. Parameters with significant *p*-values in the univariate analysis will be entered into a stepwise multivariate analysis. Deviations from Hardy-Weinberg equilibrium of individual alleles and differences in allele frequencies between the two groups will be evaluated by either the chi-square test or Fisher’s exact test where appropriate. Statistical comparisons for genotype frequencies between persons with KTD and those without KTD will be made by the chi-square test or Fisher’s exact test. Associations between allele sets or haplotypes and the risk of TDF-induced KTD will be estimated by computing odds ratios and 95% confidence intervals from multivariable logistic regressions. This analysis will include adjustments for demographic characteristics (age, sex, and BMI), baseline eGFR, duration of HIV infection, protease inhibitor therapy, and other antiretroviral treatment. All statistical analyses will be conducted using Stata 12 and R statistical software. *P* values < 0.05 will be considered statistically significant. Methods for controlling the false discovery rate and Bayesian analysis under shrinkage priors will be used when reporting the results of multivariable logistic regression.

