## Discussion

Individuals of African descent have an increased risk of developing CKD, with CKD in non-HIV individuals 3–4 times more common in Africa than in developed countries [5, 6]. In Nigeria, 38–53% of PLWHIV develop CKD [35, 36]. The high prevalence of kidney disease in sub-Saharan Africa coupled with the initiation of TDF-based regimens in PLWHIV at risk of kidney failure highlights the need to regularly screen PLWHIV for renal dysfunction, including KTD to reduce the burden of nephrotoxicity.

There has been increasing interest in the pharmacogenomics of renal drug transporters as a useful tool for identifying individuals who might be at risk of developing KTD, as it allows for a personalised approach to the use of TDF in PLWHIV on antiretroviral therapy. However, it is difficult to screen for genetic markers of KTD in resource poor areas, and to date no African study has investigated genetic markers of KTD. Moreover, previous studies on the pharmacogenetics of KTD in PLWHIV who were treated with TDF have provided diverse results [32, 33, 37]. Several factors could induce KTD, including infection, inflammation, pre-existing kidney disease, concurrent use of nephrotoxic drugs and diabetic kidney disease, and it is therefore difficult to evaluate whether KTD is exclusively caused by TDF. Thus, the role of genetic polymorphisms in drug transporter genes on TDF-induced KTD remains to be distinguished and isolated from other aforementioned risk factors for KTD, especially in individuals of African descents.

Based on this background, this study was designed to identify those risk factors that may be associated with TDF-induced KTD in Nigerian PLWHIV who are receiving a TDF regimen with suppressed viral load, and free of pre-existing kidney impairment and major comorbidities. This study also seeks to investigate the interaction between these risk factors and genetic predisposition as well as the interaction between polymorphisms in drug transporter genes and *APOL1* genetic variants.

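### Everyone studied is on TDF and no tubular marker predates it, so the study can estimate KTD among TDF users but not the TDF-induced KTD it names

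*Protocol article*

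**What the plan says.** The article names its target quantity in two ways.

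**As a drug effect.** The abstract's aim is "We aim to establish the prevalence of and risk factors for TDF-induced kidney tubular dysfunction (KTD) among HIV-I and II individuals treated with TDF", followed by "Association between TDF-induced KTD and genetic polymorphisms in renal drug transporter genes". Its Discussion paragraph promises: "This study will establish the burden and risk factors for TDF-induced KTD in Nigerians". The Statistical analysis section says: "Associations between allele sets or haplotypes and the risk of TDF-induced KTD will be estimated". The closing aims in Background, Study design, the main Discussion, and Strengths and limitations also use *TDF-induced KTD*. Setting and study population describes cases as people who *developed* KTD. Sample size and power analysis takes a reported 13% prevalence of TDF-induced KTD and uses it as the share of all TDF-treated people who will have KTD.

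**As a condition found in TDF users.** The opening of Methods/design says: "Primary outcomes of interest in this study are the prevalence of KTD and the association of polymorphisms in selected candidate SNPs". The word *induced* is absent there.

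**The population.** Setting and study population states, with follow-up counted in months: "Participants meeting the inclusion criteria will be PLWHIV, aged 18 years and above, receiving TDF-containing therapy, on regular follow up for a minimum of 3". For the comparison group it states: "The controls will be PLWHIV on a TDF regimen under regular follow up for ≥3 months". Cases and controls are also matched on TDF duration within 3 months.

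**The measurement.** Diagnostic criteria for KTD is a purely biochemical definition. The baseline laboratory data under Recruitment of participants are CD4 count, viral load, creatinine and eGFR, with no tubular marker. The eGFR used for exclusion comes from the month of enrolment.

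**The concern.** A TDF-induced quantity is a contrast: KTD with TDF against KTD without it in comparable people, or against the same people before they started. This design holds exposure constant and measures tubular function only on treatment, so it contains neither contrast.

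The article itself gives reasons why KTD in these patients need not come from TDF. Its main Discussion lists infection, inflammation, prior kidney disease, nephrotoxic drugs and diabetic kidney disease as causes, and concedes that "it is therefore difficult to evaluate whether KTD is exclusively caused by TDF". Its Background ties APOL1 variants to HIV-associated nephropathy with severe tubular damage, without reference to TDF. An APOL1 association among TDF users could therefore arise with TDF playing no part.

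At stake is what will be concluded. An all-cause prevalence could be reported as the burden of the drug, and a TDF-independent APOL1 association as a pharmacogenetic effect. Background and Discussion both present these genetics as a route to a personalised approach to TDF, so the attribution matters for how the results are used.

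**Working it through.** **1. The plan's own figures.** Inputs from Sample size and power analysis: MAF 0.19, dominant model, prevalence 13%, alpha 0.003, power 80%, OR 1.75.

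- Carrier frequency: 1 − (1 − 0.19)² = 0.344.
- Solving the baseline risk so that overall prevalence is 13% gives carrier proportions p₁ = 0.459 in cases and p₀ = 0.327 in controls.
- n per group = [z₁₋α/₂·√(2p̄(1−p̄)) + z_power·√(p₁(1−p₁) + p₀(1−p₀))]² / (p₁ − p₀)², with z values 2.968 and 0.842 and p̄ = 0.393. This gives 393. A 1:1 matched likelihood-ratio calculation gives 397. Table 1 states 398.
- Power with 400 + 400 is 81%.
- Screening: 400 / 0.13 = 3077, and 3000 × 0.13 = 390 cases, against a stated figure of about 3000.

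The sample size reproduces. It is sound for all KTD in TDF users, and it is the size for TDF-induced KTD only if KTD without TDF is zero.

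**2. What the data can separate.** Write the observed prevalence as P = b + e, where b is the KTD rate that comparable people would have without TDF and e is the excess due to TDF. The survey estimates P alone. With P = 13%, every pair from (b = 0, e = 13%) to (b = 13%, e = 0) fits the same data. Covariate adjustment does not change this, because no covariate stands in for an absent exposure contrast.

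The same holds for a SNP. An OR of 1.75 among TDF users is what one would see if the SNP acts only through TDF and all cases are TDF-induced. It is also what one would see if the SNP raises KTD risk by that factor regardless of TDF.

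**3. Illustration of size.** The background rates are assumptions; the documents give none. Attributable fraction = (13 − b)/13. Overstatement = 13/(13 − b).

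| Assumed b | TDF excess | Attributable fraction | Overstatement if 13% is called TDF-induced |
|---|---|---|---|
| 2% | 11% | 85% | 1.2 |
| 4% | 9% | 69% | 1.4 |
| 6% | 7% | 54% | 1.9 |
| 8% | 5% | 38% | 2.6 |

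**4. Illustration for a SNP that acts only through TDF.** Suppose a fraction f of cases is TDF-induced with OR 1.75, and the SNP has no effect on the rest. The carrier proportion in cases is then f × 0.459 + (1 − f) × 0.327.

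| f | Observed OR | Power, 400 + 400, alpha 0.003 |
|---|---|---|
| 100% | 1.75 | 81% |
| 85% | 1.62 | 62% |
| 60% | 1.41 | 26% |
| 40% | 1.26 | 8% |

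Mixed causation can therefore dilute a real TDF-specific effect as well as credit TDF with an effect that is not its own.

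**The case against.** The strongest defence is that the primary outcomes are already worded correctly. Methods/design speaks of KTD, not TDF-induced KTD, and parts of Study design refer to KTD in people taking TDF. This stands. A reader might infer that the primary outcomes cannot be obtained. The documents do not support that: prevalence of KTD and SNP associations with KTD among TDF users are both estimable. What cannot be obtained is the causal quantity named elsewhere.

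Second, the design does reduce competing causes. It requires a viral load below 200 copies/ml, excludes eGFR below 60, glomerulonephritis, advanced heart failure and malignancy, counts glucosuria only in nondiabetics, and adjusts for eGFR, HIV duration and other antiretrovirals. This also stands, so it would be too strong to say that nothing is done about other causes. But reducing them is not removing them. Diabetes, hypertension, hepatitis B or C, tuberculosis and nephrotoxic drugs are not exclusions; several are recorded as risk factors. That sits poorly with the Discussion's description of a sample free of major comorbidities.

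Third, the Discussion admits that attribution is difficult. The admission is partial: the same section goes on to state the aim as TDF-induced KTD. Strengths and limitations names progression, unmeasured confounding and the lack of whole-genome sequencing, but not attribution.

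Finally, the wording about future use is conditional. That is fair; how the results will be reported is a risk, not a certainty.

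**Conclusion.** The point holds as a mismatch between the stated quantity and the design. The study estimates the prevalence of KTD, and SNP associations with KTD, among TDF-treated PLWHIV. It does not estimate the TDF-caused part of that prevalence or a gene-by-TDF effect, and the passages that claim these conflict with the primary outcomes in Methods/design.

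No size can be fixed from the documents. The attributable fractions of 85% down to 38% rest on an assumed background of 2% to 8%, and on that background applying equally to TDF users. They are illustration only, as are the diluted odds ratios. A reader might take them as showing that 13% is overstated by a known factor, or that the sample size is wrong. Neither follows: the true background rate is unknown, and the sample size is right for all KTD in TDF users.

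**What to change.** - In the Abstract, the aims in Background, Study design, Sample size and power analysis, Statistical analysis, Discussion, and Strengths and limitations, replace *TDF-induced KTD* as the study's own quantity with KTD among TDF-treated PLWHIV, in line with Methods/design.
- In the case definition, replace *developed* with: have KTD at the survey.
- In Sample size and power analysis, describe the 13% as the assumed prevalence of KTD in TDF-treated people.
- Add to Strengths and limitations that neither a TDF-attributable burden nor a gene-by-TDF effect will be concluded, because there is no TDF-free group and no pre-TDF tubular measurement.
- Optionally, report KTD prevalence by TDF duration in the full cross-sectional sample, labelled as supportive only. Duration is confounded with age and HIV duration, and people taken off TDF are not sampled. A SNP-by-duration analysis in that full sample should not be promised, because the Abstract places SNP evaluation in the 400 + 400 case-control phase.

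The cost is wording, plus at most one descriptive analysis of survey data. It needs no new recruitment, which matters with 2491 participants enrolled by June 2020. The downside is a weaker headline claim.

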**Methods:**

This study has two phases. An initial cross-sectional study will screen 3000 individuals attending the HIV clinics in south-west Nigeria for KTD to determine the prevalence and risk factors. This will be followed by a case-control study of 400 KTD cases and 400 matched controls to evaluate single nucleotide polymorphism (SNP) associations. Data on socio-demographics, risk factors for kidney dysfunction and HIV history will be collected by questionnaire. Blood and urine samples for measurements of severity of HIV disease (CD4 count, viral load) and renal function (creatinine, eGFR, phosphate, uric acid, glucose) will also be collected. Utility of urinary retinol binding protein (RBP) and N-acetyl-beta-D-glucosaminidase (NAG) levels as surrogate markers of KTD will be evaluated. Genomic DNA will be extracted from whole blood and SNP analyses performed using the rhAMP SNP genotyping assays. Statistical analysis including univariate and multivariate logistic regression analyses will be performed to identify factors associated with KTD.

**Discussion:**

In spite of TDF being the most commonly used antiretroviral agent and a key component of many HIV treatment regimens, it has potential detrimental effects on the kidneys. This study will establish the burden and risk factors for TDF-induced KTD in Nigerians, and explore associations between KTD and polymorphisms in renal transporter genes as well as *APOL1* risk variants. This study may potentially engender an approach for prevention as well as stemming the burden of CKD in sub-Saharan Africa where GDP per capita is low and budgetary allocation for health is inadequate.

## Background

Nigeria bears approximately 10% of the global burden of HIV/AIDS, with approximately 130,000 newly diagnosed HIV infections and 45,000 AIDS-related deaths reported in 2020, representing a 35% decrease from 2019 [1]. According to UNAIDS, 42% of the new HIV infections occur among couples practicing ‘low risk’ sex (heterosexual), while 40% occur among high-risk populations which constitute about 1% of the general population, including female sex workers, men that have sex with men and injecting drug users [2].

Both types of the human immunodeficiency virus, type 1 and 2, are present in Nigeria; a report of the analysis of 2228 western blot results showed that 98.3% were positive for HIV-1, 0.4% were positive for HIV-2 while 0.3% were co-infections [3].

According to the study by Oko-Jaja et al. [4], the prevalence of comorbid conditions among people living with HIV (PLWHIV) includes renal disease (14.4%), hypertension (6.2%), pulmonary tuberculosis (3.4%), hepatitis-B infection (1%), diabetes mellitus (0.6%), and hepatitis-C infection (0.2%). It is increasingly recognised that individuals of African descent are at a high risk of developing renal failure [5]. Chronic kidney disease (CKD) is at least 3–4 times more frequent in Africa than in developed countries [6] and HIV infection is associated with an increased risk of renal impairment, particularly in HIV individuals with pre-existing CKD [7, 8]. People living with HIV are not only at increased risk of HIV-related kidney disease, but are also prone to other causes of CKD, including diabetes and hypertension, observed in the general population [9].

According to 2020 data, 89% (comprising of 55% adults and 35% children) of those with a HIV positive diagnosis in Nigeria are accessing ART, and out of these, 42% were virally suppressed [1, 10]. Tenofovir disoproxil fumarate (TDF) is one of the most frequently used ART [11]. Currently, more than 80% of PLWHIV in Nigeria were receiving a TDF-based regimen, as Nigeria adopted TDF-based ART as the first-line treatment for HIV in 2014 [1, 12]. Whilst the initial randomised control trials suggest good overall safety for TDF, numerous subsequent studies have shown issues with the renal safety profile, including KTD in various study settings [13]. Furthermore, TDF has also been associated with a wide range of other manifestations of renal impairment than KTD such as low eGFR and rapidly declining eGFR. Globally, the reported incidence of TDF-induced nephrotoxicity ranges between 0.7 and 22% [14, 15]. Likanonsakul et al. [16] in their study reported that approximately 20% of PLWHIV receiving TDF in Thailand had β2-microglobulinuria, a marker of tubular dysfunction. Various risk factors have been associated with KTD including co-morbidities (such as hepatitis C, diabetes mellitus), low body weight, older age, concomitant administration of potentially nephrotoxic drugs, low CD4 count and duration of therapy [17].

In West Africa, a study carried out among a Ghanaian population of PLWHIV taking TDF showed that the prevalence of creatinine clearance less than 60 ml/min/1.73m^2^, dipstick proteinuria and asymptomatic renal tubular dysfunction was 7, 37 and 15% respectively [18]. In Nigeria, little is known about the prevalence of TDF-induced KTD. It is difficult to screen for this complication in resource-poor settings, and very few Nigerian studies have investigated markers of TDF-induced KTD. A study of 57 PLWHIV in Port Harcourt in southern Nigeria suggested an increased burden of KTD in individuals exposed to the TDF regimen. Results showed that after 12 weeks of exposure, 14% of PLWHIV exposed to TDF developed phosphaturia [19].

Renal tubular transporter proteins, including organic anion transporters (OAT) and multidrug resistance-associated proteins (MRP), otherwise known as the ATP binding cassette (ABC) superfamily, have been implicated in the uptake and secretion of TDF in the proximal renal tubule. Genetic variants in renal drug transporters are believed to confer susceptibility to TDF-induced KTD among Europeans [20], but an association between KTD and polymorphisms in genes encoding kidney drug transporters has not been previously investigated in African populations.

The mechanisms underlying the increased incidence of tubular injury in PLWHIV treated with TDF remain to be fully elucidated. Apolipoprotein L1 (APOL1), which accounts for almost 70% of the excess risk of kidney disease in individuals of African descent, is expressed in the proximal tubular cells in normal kidneys [21]. Approximately 87% of PLWHIV with CKD in Nigeria had 2 *APOL1* risk alleles, and previous studies have showed that *APOL1* genetic variants are strongly associated with HIV-associated nephropathy, a rapidly progressing kidney disease with severe tubular damage [22, 23]. Risk variants of *APOL1* act via a gain of injury or toxic activity on podocytes and other cells in the kidney including proximal tubular epithelial cells [21], thus *APOL1* renal risk alleles may contribute to the severity of TDF toxicity through this pathway.

In spite of TDF being the most commonly used antiretroviral agent and a key component of many HIV treatment regimens, it has been shown to have detrimental effects on the kidneys [13]. Tenofovir alafenamide (TAF), a novel TDF analogue with decreased renal injury, was recently approved by the US Food and Drug Administration [24], but the clinical significance of the long-term superior renal safety profile of TAF over TDF remains uncertain. As yet, there are no data for TAF safety in pregnancy, tuberculosis coinfection, or low CD4 count. It remains to be seen whether the substitution of TDF with TAF will make a justifiable incremental claim on scarce HIV treatment resources in the near future. There is increasing interest in the pharmacogenomics of renal drug transporters as a useful tool for identifying individuals who might be at risk of developing KTD, as it allows for a personalised approach to the use of TDF in PLWHIV on antiretroviral therapy.

This study aims to establish the burden and risk factors for TDF-induced KTD in Nigerians, and explore associations between KTD and polymorphisms in the renal transporter genes as well as *APOL1* risk variants. The study may potentially engender an approach for prevention as well as stemming the burden of CKD in sub-Saharan Africa particularly Nigeria, where GDP per capita is low and budgetary allocation for health is inadequate.

We hypothesise that KTD is common among adult PLWHIV in Nigeria who are receiving TDF-based antiretroviral therapy, and additive contributions from polymorphisms in kidney tubular transporters as well as *APOL1* genetic variants may be associated with the risk of KTD in Nigerians treated with TDF. Further, we hypothesise that the additive contribution from *APOL1* risk alleles would predispose to and enhance the severity of TDF toxicity and that the concomitant use of protease inhibitor may additively influence the susceptibility for severe TDF-induced nephrotoxicity. This paper describes the design and methodology for this study that aims to determine the prevalence and risk factors for TDF-induced KTD in PLWHIV in Nigeria.

